# L-arginine and aged garlic extract for the prevention of migraine: a study protocol for a randomised, double-blind, placebo-controlled, phase-II trial (LARGE trial)

**DOI:** 10.1186/s12883-023-03149-y

**Published:** 2023-03-27

**Keywords:** Aged garlic extract, L-arginine, Chronic frequent episodic migraine, Photosensitivity, Randomised controlled trial, Retinal imaging, Vascular tone.

## Abstract

**Background:**

Migraine is a common and distressing neurological condition characterised by recurrent throbbing headaches, nausea and heightened sensitivity to light and sound. Accumulating evidence suggests that cerebral arteries dilate during migraine, causing distal microvessels to constrict, which could activate nociceptors and cause onset of headache pain. If so, preventing or attenuating chronic microvascular constriction, and promoting a dilatory phenotype, may reduce frequency and/or severity of migraines. The primary aim of the L-Arginine and Aged Garlic Extract (LARGE) trial is to investigate whether oral treatment with dietary nutraceuticals, L-arginine and aged garlic extract (AGE), both systemic vasodilatory agents, will alleviate migraine frequency, duration and severity in adults with chronic frequent episodic migraines.

**Methods:**

The study is a randomised double-blind placebo-controlled phase-II single-site clinical trial conducted in Perth, Australia. The target sample is to recruit 240 participants diagnosed with chronic frequent episodic migraines between 18 and 80 years of age. Participants will be randomised to one of four treatment groups for 14 weeks (placebo induction for 2 weeks, followed by 12 weeks on one of the respective treatment arms): placebo, L-arginine, AGE, or a combination of L-arginine and AGE. The doses of L-arginine and AGE are 1.5 g and 1 g daily, respectively. The primary outcome is to assess migraine response using change in migraine frequency and intensity between baseline and 12 weeks. Secondary outcomes include the impact of L-arginine and/or AGE on photosensitivity, retinal vessel changes, and blood biomarker concentrations of vascular tone, following a 12-week intervention.

**Discussion:**

The protocol describes the oral administration of 2 nutraceutical-based interventions as possible prophylactic treatments for chronic frequent episodic migraines, with potential for direct clinical translation of outcomes. Potential limitations of the study include the fixed-dose design of each treatment arm and that in vivo neuroimaging methods, such as magnetic resonance imaging (MRI), will not be conducted to determine putative cerebro-vasodilatory changes to coincide with the outcome measures. Dose-response studies may be indicated.

**Trial registration:**

The trial was retrospectively registered with the Australian New Zealand Clinical Trials Registry ACTRN12621001476820 (Universal Trial Number: U1111-1268-1117) on 04/08/2021. This is protocol version 1, submitted on 25/11/2022.

**Supplementary Information:**

The online version contains supplementary material available at 10.1186/s12883-023-03149-y.

## Background

Migraine is one of the most common and disabling neurovascular disorders, affecting more than one billion people worldwide [1]. Considered the third most costly neurological disorder to treat, the socio-economic impacts of migraines are substantial [2, 3]. The understanding of the pathophysiology and aetiology of migraines has increased substantially over the past few decades, with emergence of new therapeutic approaches. However, appropriate access and use of current therapeutic options are scant, as migraine treatments are often related to adverse effects, and are unavailable to many patients due to strict prescribing guidelines [4–6].

The prevailing dogma of migraine suggests that vasodilatation of large cerebral arteries contributes to pain associated with migraines. We provide an alternate hypothesis for the pathophysiology of vascular-based migraines, whereby stress-induced heightened sympathetic tone results in a chronically constrictive cerebral microvascular phenotype [7]. Reduced central parenchymal blood flow could then activate nociceptors and cause headache onset. Thus, we put forward the hypothesis that prevention or attenuation of chronic microvascular constriction reduces the frequency or severity of vascular-mediated headaches. There are numerous limitations with current migraine medications, including medication overuse that can paradoxically induce headache [8, 9], many are vasoconstrictive which is a contraindication for patients with cardiovascular complications [10–12], invasive subcutaneous administration, high costs, and regulatory restrictions [11, 13]. Accordingly, benign vasodilating alternatives to prevent and treat patients with vascular-induced headaches need to be urgently considered.

L-arginine (2-amino-5-guanidinopentanoic acid, arginine) and aged garlic extract (AGE) are two oral nutraceutical agents that have been used to improve several cardiovascular disease risk factors via vasodilatory mechanisms [14–21]. However, neither have been investigated as a prophylactic option to treat chronic frequent episodic migraines. Briefly, through enhanced biosynthesis of endothelial nitric oxide (L-arginine) or increasing systemic vasodilatory prostaglandins (AGE) amongst other anti-inflammatory and antioxidant properties, L-arginine and AGE are likely to be efficacious in attenuating migraine severity/frequency induced by cerebral microvascular constriction. A significant advantage of these two nutraceuticals over current conventional migraine drug treatments is that the safety profile of both agents has been widely documented and well-tolerated in the context of cardiovascular indications with minimal side effects.

Here, we detail the study protocol for the ‘L-Arginine and Aged Garlic Extract (LARGE) for the Prevention of Migraine’ trial. The study is a 12-week, phase-II, single-site, randomised, double-blind, parallel-group-design, placebo-controlled trial, investigating the efficacy of either oral L-arginine, AGE or a combination of these nutraceuticals in adults with chronic frequent episodic migraines. Key outcome measures include frequency of migraines attacks and intensity of headache pain. Additional exploratory outcome measures include changes in photosensitivity, retinal vascular diameter, and blood biomarkers of vascular tone.

## Objectives

We are trying L-arginine and AGE for the first time for headaches, based on our proposed underlying mechanism and these nutraceuticals’ vascular applications in the past. The rationale for this study is that migraine may be caused by sympathetically induced and/or compensatory-to-vasodilation capillary constriction, leading to insufficient blood flow in the brain relative to increased energy demands in times of stress, and the triggering of trigeminal nerve endings via large-vessel dilation. We are investigating whether the known capillary-dilating agents, L-arginine and/or aged garlic extract, prevent the capillary constriction we propose underlies the headache. Therefore, our primary measure will be alleviation in migraine frequency and/or severity via self-reported subjective questionnaires; and our secondary measures will determine expansion of brain capillaries via blood biomarkers of systemic vascular tone and via retinal optical coherence tomography angiography. An additional secondary measure will be a photosensitive test using a brightening light source, to determine difference in this major migraine symptom, also before and after treatment.

The primary objective of this study is to evaluate the impact of oral 1.5 g/day L-arginine, 1 g/day AGE, or a combination of the two nutraceutical doses, on reducing migraine frequency and severity, compared with placebo, in adults with chronic frequent episodic migraines, over a 12-week intervention period. The secondary objectives are to measure the independent and combined effects of each intervention on physiological vasodilation in the retinal vessels, onset of photosensitivity, blood biochemical markers of vascular tone, and to evaluate the impact on quality of life, in adults with chronic frequent episodic migraines.

## Methods/Design

The methods reporting of this study follow the recommendations of the Standard Protocol Items: Recommendations for Interventional Trials Statement [22].

### Trial design

This is a single-site, randomised, double-blind, parallel-group-design, placebo-controlled, phase-II clinical trial on the efficacy, safety and tolerability of oral L-arginine and/or AGE in 18-80-year-old individuals with chronic frequent episodic migraines, based in Perth, Western Australia (WA). Study participants and members of the research team will be blinded to randomisation of the intervention treatments.

The maximum study duration is 14 weeks with a 2-week placebo run-in followed by a treatment period of 12 weeks. Eligible participants will be randomised to one of four parallel treatment groups in a 1:1:1:1 ratio, using permuted block randomisation: placebo, L-arginine, AGE, and combined L-arginine and AGE. Factoring for up to 20% drop-out rate, we aim to recruit 240 participants with up to 60 individuals randomised to each of the four treatment groups. Figure 1 shows an overview of the study design for the LARGE trial. The trial is registered through the Australian New Zealand Clinical Trials Registry (ACTRN12621001476820).

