### Statistical analysis

#### Sample size and statistical power

We propose an RCT with a factorial treatment structure. This design is efficient and allows the estimation of both the main effects of L-arginine and AGE, and the interaction between L-arginine and AGE. This design with two factors at 2 and 2 levels has 4 arms/groups (treatment combinations). A total of 240 individuals are required to provide 60 subjects per group. This design achieves 87% power when an F-test is used to test factor L-arginine at a 5% significance level with the effect size of 0.2; achieves 87% power when an F-test is used to test factor AGE at a 5% significance level with the effect size of 0.2; and achieves 87% power when an F-test is used to test the L-arginine*AGE interaction at a 5% significance level with the effect size of 0.2. Cohen’s Effect Size Table [45] provides the interpretation of effect sizes as: Small: 0.1; Medium: 0.25; Large: 0.40. Our research study can therefore detect between small and medium effect sizes between each of the main effects and interactions. An estimated effect size of 0.2, used in the sample size calculation for testing the main effects and interaction, was obtained from our preliminary data. Assuming a dropout rate of 20%, a total of 300 participants will be initially recruited into the study, with 75 participants in each of the 4 treatment combinations.

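### The protocol recruits 240 in two places and 300 in a third, and at its planned 20% dropout the stated 87% power holds only with 300.

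*Protocol article*

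**What the plan says.** The article gives the trial's size in three places.

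- **Abstract, Methods:** "The target sample is to recruit 240 participants". Dropout is not mentioned here.
- **Trial design:** "Factoring for up to 20% drop-out rate, we aim to recruit 240 participants with up to 60 individuals randomised" to each of the four groups, in a 1:1:1:1 ratio. The 20% loss is already inside the 240.
- **Sample size and statistical power:** "A total of 240 individuals are required to provide 60 subjects per group". With that number, the section claims 87% power for each of three F-tests (the L-arginine main effect, the AGE main effect and their interaction) at the 5% level and an effect size of 0.2. It then adds: "Assuming a dropout rate of 20%, a total of 300 participants will be initially recruited into the study", with 75 in each of the four treatment combinations.

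**The concern.** The figure of 240, or 60 per group, is used in two roles. In the Trial design section it is the number entering the trial, before losses. In the sample size section it is the number the power calculation needs, and losses are added on top. At a dropout rate of 20% it cannot be both.

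The recruitment target decides when enrolment closes and how long the randomisation list and the capsule supply must be. 300 is 25% more than 240 (300/240 = 1.25). If enrolment stops at 240, the trial has met its target by the abstract and the Trial design section, but is 60 short by the sample size section. In the first case the 87% quoted for all three tests would not be what the design delivers at the dropout it plans for.

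**Working it through.** **Inputs, all from the sample size section unless noted**

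- 2 × 2 factorial with four cells, so each main effect and the interaction has 1 numerator degree of freedom.
- Effect size 0.2. The section interprets it on the scale 0.1 / 0.25 / 0.40, which is Cohen's f.
- Significance level 0.05, with no multiplicity adjustment in the power statement.
- Required number 240 (60 per group); stated power 87%.
- Dropout 20% (the Trial design section says up to 20%).
- Equal allocation (Trial design section).

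**Formula.** Power = P(F′ > F_crit), where F′ is non-central F with df1 = 1, df2 = N − 4 and non-centrality λ = N × f², N is the number analysed, and F_crit is the 95th percentile of the central F with the same degrees of freedom.

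**Step 1: reproduce the stated power.** N = 240: df2 = 236, λ = 240 × 0.04 = 9.60, F_crit = 3.881, power = 86.99%. This agrees with the stated 87%, so the 240 in the power statement is the number analysed.

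**Step 2: reproduce the stated recruitment figure.** 240 / (1 − 0.20) = 300, and 300 / 4 = 75 per group. Both agree with the sample size section, which is therefore consistent within itself.

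**Step 3: apply the same dropout to the other target.** 240 × (1 − 0.20) = 192, and 192 / 4 = 48 per group. N = 192: df2 = 188, λ = 192 × 0.04 = 7.68, F_crit = 3.891, power = 78.7%. The type II error goes from 13.0% to 21.3%.

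**Step 4: effect size needed.** Solving the same formula for f with N = 192 and power 87% gives f of about 0.224, against the planned 0.2.

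**Step 5: sensitivity to dropout, with 240 recruited**

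| Dropout | Analysed | Power |
|---|---|---|
| 0% | 240 | 87.0% |
| 5% | 228 | 85.2% |
| 10% | 216 | 83.3% |
| 20% | 192 | 78.7% |

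The stated figure is reached only with no loss at all.

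**Step 6: can a definition reconcile the two?** One could suppose that 300 are recruited, 60 are lost in the placebo run-in, and 240 are randomised. The text does not allow this. The schedule of assessments (Table 2) and the Allocation section place allocation at visit 1, before the run-in. The sample size section puts 75 in each treatment combination. The abstract and the Trial design section both apply the word recruit to 240.

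**The case against.** The strongest points on the other side concern how firmly the loss of power can be stated. The contradiction itself is not in dispute.

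- **Up to 20% is an upper bound.** With 240 recruited, power lies between 78.7% and 87.0%, depending on the actual loss. This is right as far as it goes. But the sample size section plans on 20%, so 78.7% is the matching planning figure.
- **The planned analysis is not a plain F-test.** The statistical methods section plans ANCOVA with the baseline value as covariate, and mixed models. Data collected before withdrawal are kept, so some dropouts may contribute. If 0.2 is an unadjusted effect, which the article does not say, f becomes 0.2 / √(1 − r²) for a baseline–outcome correlation r. At 192 analysed, power would be 82.4% for r = 0.3 and 88.9% for r = 0.5, and about 87% for r = 0.45. These correlations are assumptions. The article gives none and its power calculation counts no such gain. The exclusion of poorly compliant participants (Intervention description and adherence section) works the other way.
- **Multiplicity.** The statistical methods section sets a family-wise error rate of 0.05. If that covered the three factorial tests by Bonferroni (an assumption, since the family is not defined), power would be about 75% at 240 analysed and 64% at 192. Any restated figure should therefore say that it is unadjusted.
- **The abstract does not mention dropout.** True. Only the Trial design section says that the 240 already allows for it. The abstract conflicts with 300 all the same.
- **The sample size section may be the one that governs.** It is the dedicated section and its figures reproduce. If it governs, the repair is wording in two summary passages. But nothing in the article says that it does.

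These points qualify the size of the loss. None removes the conflict between 240 and 300.

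**Conclusion.** The concern holds. The article states two recruitment targets, 240 and 300, that cannot both be true, and nothing in it reconciles them. On the protocol's own inputs (f = 0.2, unadjusted 5% level, 1 degree of freedom, 20% dropout with dropouts not analysed), the 87% power follows from 300 recruited and 240 analysed. With 240 recruited it falls to 78.7%, a loss of about 8 percentage points that applies equally to both main effects and the interaction. The size of the loss depends on those inputs; the inconsistency does not. Because this is a core design number and it determines when enrolment closes, it must be corrected.

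**What to change.** State one recruitment target, in the same terms, in the abstract, the Trial design section and the sample size section, and say in each whether the number is recruited or analysed. Two versions are consistent:

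- **300 recruited (75 per group), 240 analysed (60 per group), 87% power.** Change the abstract and the Trial design section from 240 to 300. The cost is 60 more participants than those passages announce, with the matching capsule supply and randomisation list.
- **240 recruited (60 per group), 192 analysed (48 per group) at 20% dropout.** Remove the 300 from the sample size section and restate power there as about 79% at f = 0.2, unadjusted for multiplicity or baseline covariates. No extra participants are needed; the cost is a less favourable power statement.

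The choice should follow the target the ethics committee approved, and should be fixed before results are known.

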### Study setting and recruitment

The single-site trial will be based in Perth (WA). Study visits will be completed at the Sarich Neuroscience Research Institute (SNRI), Nedlands (WA), with retinal imaging conducted at the Lions Eye Institute (LEI), Nedlands (WA) (adjacent to SNRI). To reach the targeted sample size, potential participants will be recruited through advertising and editorials on social media, print, radio and/or television; correspondence and promotions via not-for-profit organisations and research partners; and website content.

Prospective participants will be informed that participation is voluntary, and that withdrawal of consent is possible at any time without having to provide justification. All relevant information will be disclosed during the consent procedure with the opportunity to clarify questions with the investigator team. Enrolment is only possible after written informed consent is obtained (see Appendix 1 for participant Information Sheet and Consent Form).

### Eligibility criteria

The eligibility criteria for the participants in this study are listed in Table 1 below. The inclusion criteria must be fulfilled, and the exclusion criteria must not apply. Eligibility will be verified by delegated research personnel at the inclusion/consent visit.

**Table 1 Tab1:** LARGE trial inclusion and exclusion criteria

Inclusion criteria	Exclusion criteria
1. Migraine (with or without aura) diagnosed at least 1 year ago 2. Migraine onset occurred before 50 years of age 3. Adult males and females, aged 18–80 years (inclusive) at screening 4. 2–6 migraine episodes and fewer than 6 ‘other’ headache types per month, averaged over the previous 3 months 5. Able to differentiate between migraine and ‘other’ headache types 6. Able to commit to taking oral capsules once a day for 14 weeks 7. Able to fill out paper daily migraine diary over 14 weeks	1. Taking medications/drugs that affect vascular tone or blood pressure 2. Continuous residual headaches 3. Headache disorder or facial pain disorder other than migraine 4. Change in migraine treatment in previous 3 months 5. Taking > 2 migraine-prevention drugs 6. L-arginine tablets or aged garlic extracts in previous 3 months 7. Possibility of pregnancy or breastfeeding during study 8. Adverse reactions to food containing L-arginine or garlic 9. Clinical reports of kidney/liver dysfunction 10. Known risks of bleeding or coagulopathy, or currently on blood-thinning medications 11. Cancer, haemochromatosis or diabetes 12. Severe psychiatric disorder or other neurological disorders 13. Acute/chronic pain disorders, infections, cardiovascular or cerebrovascular disease 14. Poorly controlled depression or anxiety 15. Antipsychotic or antidepressant medications/drugs over past 3 months 16. Low blood pressure or complications arising from it 17. Diagnoses other than migraine as primary cause of headaches 18. Changes in digestive system over past few months 19. Headaches cause fainting or other medical emergencies 20. Substance abuse/dependence/addiction in previous 3 months 21. Procedure or injection to treat migraine over past 3 months 22. Implanted or external nerve stimulator to treat migraines 23. Pain medications on most days a week for headaches 24. Opioid medications each day for chronic pain 25. History of overusing medications 26. History of eye pathology, surface disorder, surgery (except cataract extraction), or injury 27. Difficulty seeing clearly (with glasses or contact lenses, if required) 28. History of diabetes, hypertension, collagen vascular disease, vasculitis, or renal disease/failure 29. Smoke > 1 pack of cigarettes a day 30. Disorders of the optic nerve or retina 31. Reasons that retinae may not be clearly viewed 32. Poor image perception due to cataract or unstable fixation 33. Anaemia or iron deficiency 34. Participation in concurrent research trial

**Fig. 1 Fig1:**
[figure not shown]
Overview of flow of participants. L-arg = L-arginine; AGE = aged garlic extract; OCTA = optical coherence tomography angiography. Participant self-report long-term questionnaires consist of the Migraine-Specific Quality-of-life Questionnaire (MSQ), Short-Form McGill Pain Questionnaire (SF-MPQ), Leiden Visual Sensitivity Scale (L-VISS), and Visual Light Sensitivity Questionnaire – 8 (VLSQ-8). Migraine diaries are completed daily and weekly over the 2 and 12 weeks between visits

### Study intervention

#### Intervention description and adherence

This study consists of 2 phases, including: (a) a 2-week placebo run-in phase (week − 2 to 0); (b) a 12-week treatment phase (day 0 to day 84). The Diener and Tassorelli guidelines suggest that a 4-8-week screening phase is ideal to ensure diagnostic migraine criteria are met for both episodic and chronic migraines [23, 24]. However, since participants could benefit from 3 months’ treatment without a high attrition rate, 4–8 weeks’ placebo would already take up half the investigation time for each participant. We are relying on participant numbers to compensate to power the study, and we have already ensured diagnostic criteria are met, as all participants must have confirmation from a physician or neurologist that they have migraine. We have included the extensive list of eligibility criteria, including frequency of migraines participants must have to be included in the trial. Participants are asked to report any adverse effects that arise from the treatment, at absolutely any point during their time in the trial. They are contacted one week after each of visits 1 and 2 to reinforce this and to check treatment compliance. Leftover capsules are counted at the end of each participant’s 2 and 12 weeks, to check placebo and verum treatment compliance, respectively.

Once individuals are deemed eligible according to the inclusion and exclusion criteria listed in Table 1, participants will be asked to provide written consent and will be enrolled into the trial. At the consent visit (visit 1), participants will be asked to provide basic demographic information, complete medical and migraine history (i.e., duration of migraine, age of onset, monthly migraine frequency), current medication, menstrual status if applicable, and medical history. Baseline demographic and anthropometric measures were adapted from the National Institute of Neurological Disorders and Stroke Common Data Elements (www.commondataelements.ninds.nih.gov) and the PhenX toolkit (https://www.phenxtoolkit.org/), respectively. During this visit, participants will be instructed on how to fill out the daily and weekly migraine diaries. All participants are required to undergo a 2-week placebo run-in and are required to take oral placebo capsules for 2 weeks (5 capsules per day). Thereafter, at visit 2 (baseline), a 12-week supply of the respective randomised treatment will be dispensed to each participant; 5 capsules a day for 12 weeks (placebo; L-arginine; AGE; combination of L-arginine and AGE). Participants are contacted one week following commencement of treatment, to discuss any potential adverse events and treatment compliance.

Each participant will be provided with a paper-based diary to improve adherence of all groups (see Appendices 2 and 3). Treatment efficacy in terms of headache pain, severity and frequency will be evaluated by a standardised daily migraine diary (Appendix 2) and a summarising weekly migraine diary to track clearer long-term progress (Appendix 3). A capsule information sheet is dispensed with the intervention capsules to provide details instructions on missed doses where relevant. Similar to the placebo run-in, participants will be required to return capsule bottles at the end of the 12-week intervention to determine adherence to treatment. Poorly compliant participants will be excluded from subsequent analyses.

Visit 3 will be an exact replica of visit 2, with the difference that no further capsules/diaries will be given, and the visit-1 long-term questionnaires will have been filled out again to compare with the results of the visit-1 ones. Blood biomarkers, photosensitivity tests and retinal scans will be compared between visits 2 and 3 to test differences due to treatment over the 12 weeks.

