### Primary and secondary outcomes

#### Primary outcomes

The primary objective of the LARGE trial is to evaluate the effectiveness of oral supplementation of L-arginine, AGE or the combined treatment of oral L-arginine and AGE, in reducing the severity and frequency of migraine attacks in chronic frequent episodic migraines in adults. By chronic frequent episodic migraineurs, we include both episodic and chronic, as well as uncertain: from published official guidelines, some clinical trial participants may not fit neatly into having episodic or chronic migraines, and/or into with or without aura, but they are nonetheless included [25]. In accordance with the International Headache Society guidelines for RCTs in preventative treatment of episodic migraines in adults [23], the differences in the mean number of migraine episodes per month, between baseline (visit 2) and end of study (EoS; 12 weeks treatment, visit 3), will be determined as the primary outcome measure assessed by a standardised daily migraine diary (Appendix 3). Migraine frequency will be measured not just within each migraine day, but the number of migraine occurrence days over the weeks. From the daily migraine diaries, treatment efficacy will be evaluated by the mean change in outcome measures between baseline and EoS within each group, and thereafter compared with changes between each intervention group. Primary outcomes collated from the diaries include: (a) mean number of migraine episodes per month (migraine frequency); (b) mean number of migraine days per month; (c) mean number of moderate-or-severe migraine days per month; (d) mean duration of each migraine episode (hours) per month; (e) mean number of acute migraine medication doses per month; and (f) number and type of self-reported adverse events per month. We will not measure migraine episode duration, because the participant is able to use an abortive drug at any point, and sleep intervals can disrupt countability of each episode.

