### Blinding

Although participants will be blinded to treatment allocation, we will inform them of the general nature and composition of the treatment prior to their participating. The investigator team will be blinded as to which treatment we are giving which participant, during the 12 intervention weeks. Only the statistician and pharmacist will not be blinded as to which participant receives which treatment, as they will be handling the randomisation schedules linking identification numbers to participant names. In case of emergency (an adverse event sustained by the participant, which requires medical treatment to know which study treatment has been given), the investigator will break the seal and be unblinded as to which treatment the participant has received. This will immediately be reported back to the investigator team and the HREC. The participant always has the option of dropping out of the trial.

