Since older subjects also tend to use polypharmacy, any unforeseen interaction effects (despite having checked for potential contraindicated drug interactions in the eligibility criteria) should come to light. Our treatment is an oral preventive which is non-invasive, and would hopefully preclude the need for combination therapy in treatment-refractive populations with a vasoconstrictive migraine aetiology. Combination therapy generally increases risk of adverse effects, and it is difficult to ascertain which drug each effect may come from and may need to be withheld [47]. We use both subjective (diaries and questionnaires) and objective measures (vascular tone, photosensitivity and blood markers) to track migraine progress longitudinally in each participant, with a placebo wash-in to further increase reliability of results. The nutraceutical agents are mildly vasodilatory, hence are not contraindicated for patients with pre-existing vasoconstrictive issues, nor should they pose a danger to patients with hypotension (we also measure blood pressure at each visit). The 2 × 2 group schedule allows a placebo control, as well as checking for interaction effects when both nutraceuticals are simultaneously given. Reported well-tolerated doses of L-arginine and AGE, considered for cardiovascular disease risk, serve as a useful guide to explore the putative efficacy of L-arginine and AGE for prevention/treatment of vascular-associated migraine.

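### The instruction to report adverse effects arising from the treatment is narrower than the adverse-event outcome it helps to feed, so events not linked to the capsules may be missed

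*Protocol article*

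**What the plan says.** Three statements in the protocol article bear on what a participant is asked to report.

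- **The instruction** (Intervention description and adherence, first paragraph): "Participants are asked to report any adverse effects that arise from the treatment, at absolutely any point during their time in the trial". It is followed by: "They are contacted one week after each of visits 1 and 2 to reinforce this and to check treatment compliance".
- **The on-treatment contact** (same section, in the account of visits 1 and 2): "Participants are contacted one week following commencement of treatment, to discuss any potential adverse events and treatment compliance".
- **The outcome** (Primary outcomes): item (f) in the list drawn from the diaries is the "number and type of self-reported adverse events per month".

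Three others show what the safety data are for. Trial design names safety and tolerability, beside efficacy, as subjects of the trial. Data collection and management lets the principal investigator end the trial, giving unforeseen adverse events as an example, and says that ethics approval did not require a formal data-monitoring committee. The Discussion, on older participants who take several medicines, says that "any unforeseen interaction effects (despite having checked for potential contraindicated drug interactions in the eligibility criteria) should come to light".

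**The concern.** The instruction depends on cause; the outcome does not. A participant blinded to four arms cannot know what arises from the treatment. To follow the instruction as worded, that person must first decide whether a symptom came from the capsules, and report it only if the answer is yes or perhaps.

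That decision filters out the events the trial most wants to find. A participant who knows the general composition of the treatment may readily connect a stomach upset with garlic, but has little reason to connect an unexpected symptom, or an interaction with another medicine, with the capsules. If such events go unreported, outcome (f) counts fewer events than occurred, the comparison of arms on safety loses sensitivity, and the investigator who may stop the trial for unforeseen events sees fewer of them.

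**Working it through.** **1. The statements side by side**

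| Place in the protocol article | Term used | Conditional on cause? |
|---|---|---|
| Intervention description and adherence, instruction | adverse effects | Yes, they must arise from the treatment |
| Same section, contacts after visits 1 and 2 | reinforce the instruction | Yes, by reference |
| Same section, contact one week into treatment | any potential adverse events | No |
| Primary outcomes, item (f) | self-reported adverse events | No |

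The contact one week after visit 2 is the contact one week into treatment, because treatment is dispensed at visit 2. The article therefore describes one contact in two ways: as repeating a request limited by cause, and as an open discussion. The two descriptions need to be reconciled. The contact after visit 1 falls in the placebo run-in. Allocation describes it only as a text to check progress with the capsules.

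**2. Is there a figure to reproduce?**

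No. The article gives no adverse-event rate, no reporting fraction and no power target for (f). What follows is an illustration. The true rates p and the reported fraction r are assumptions; the only input from the article is 60 participants per group (Sample size and statistical power).

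**3. Chance that an arm yields at least one report**

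Formula: 1 − (1 − p·r)^60. For p = 0.02 and r = 1: 1 − 0.98^60 = 0.70. For p = 0.02 and r = 0.5: 1 − 0.99^60 = 0.45.

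| True rate p | r = 1 | r = 0.75 | r = 0.5 | r = 0.25 |
|---|---|---|---|---|
| 2% | 0.70 | 0.60 | 0.45 | 0.26 |
| 5% | 0.95 | 0.90 | 0.78 | 0.53 |
| 10% | 0.998 | 0.99 | 0.95 | 0.78 |

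**4. Power to tell two arms apart**

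Two-sided 5% test of two proportions, n = 60 per arm, reported rates a = p1·r and b = p2·r, mean m = (a + b)/2:

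power = Φ{ [ |a − b| − 1.96·√(2m(1 − m)/60) ] / √( [a(1 − a) + b(1 − b)]/60 ) }

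For true rates of 10% v 30%:

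- r = 1: (0.200 − 1.96 × 0.0730)/0.0707 = 0.80, power 0.79
- r = 0.75 (7.5% v 22.5%): power 0.64
- r = 0.5 (5% v 15%): (0.100 − 1.96 × 0.0548)/0.0540 = −0.14, power 0.45
- r = 0.25 (2.5% v 7.5%): power 0.24

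**5. What the figures show**

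Both arms are scaled by the same r, so step 4 shows loss of sensitivity and nothing about bias between arms. Neither step shows that r is below 1 in this trial. They show what would follow if the wording suppressed reports.

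**The case against.** The case against has several parts, and much of it stands.

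- **The instruction does not exclude other reports.** It says nothing like only, and its emphasis on reporting at any time is open in tone. This stands: a reader might infer that participants are barred from reporting anything else, and the text does not say so.
- **Outcome (f) comes from the diaries, and the diary forms are in appendices that are not shown.** They may ask for every event. This stands: a reader might infer that (f) counts only what participants attribute to the capsules, and the article does not establish that. If the diary does ask broadly, however, the instruction conflicts with it and needs the same correction.
- **The article may only paraphrase what participants read.** The information sheet is not shown. This limits how firmly one can speak about practice. It does not remove the conflict between statements that the article itself makes.
- **Expectation should be similar in all arms.** Under Blinding the article says of participants that "we will inform them of the general nature and composition of the treatment prior to their participating", but this applies to everyone, and Supply of intervention says the capsules are identical and all lightly scented with garlic. This stands against the tempting inference that the comparison of arms is biased by guessed allocation. The documents do not show differential reporting.
- **Blood pressure is measured at each visit**, according to the Discussion, and does not depend on attribution. True, but it covers one sign.
- **The illustration uses large differences.** At 10% v 4% with every event reported, the formula above gives power of only 0.25 at 60 per arm, so full reporting would not make such a comparison reliable. This is fair, and is a reason to give weight to the chance of seeing an event at all (step 3) as well as to between-arm power.

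**Conclusion.** The point holds as an inconsistency with a plausible cost. The stated instruction ties reporting to perceived cause, the two week-1 contacts are said to reinforce it, and neither outcome (f) nor the other description of the on-treatment contact has that condition. If participants follow it literally, events they do not connect with the capsules may be missed, which works against the safety aim and against finding unforeseen effects. The likely direction is lower counts and reduced sensitivity in all arms.

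The size cannot be stated. The illustrative figures rest on assumed event rates and reporting fractions. Under-reporting itself is a risk created by the wording and is not demonstrated by the documents. The change is worth making because (f) is listed among the primary outcomes and the correction is nearly free.

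**What to change.** Reconcile the instruction with outcome (f) and with the open description of the on-treatment contact:

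1. In the instruction, and at both week-1 contacts, ask participants to report any unfavourable symptom, illness or event, whether or not they think the capsules caused it.
2. Record the participant's view of relatedness as a separate item, so that the information is kept without acting as a filter.
3. Analyse (f) on all reported events. Recruitment began in May 2021, so flag events collected before the change, allowing the two periods to be examined separately.
4. Check that the diary forms carry no condition on cause, and align them if they do.

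The cost is the rewording of an instruction, its use at two contacts, and one added data item. The downside is a somewhat higher event count in every arm, with more events that prove unrelated. Events reported before and after the change will not be fully comparable, which is why the flag is needed.
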